#### Intervention description

EFMT is a group intervention traditionally consisting of eight weekly in-person group meetings of 2.5 h, with group sizes of between 10 and 12 participants. Due to COVID-19 restrictions, EFMT will be delivered by Zoom to groups of six participants and weekly meetings will be shortened to 1.5 h to reduce Zoom fatigue, a phenomenon noted in popular media [40, 41]. For modification to video-delivery of the intervention, the number of participants has been decreased from 10 to 12, to six to provide adequate time for all components of the intervention to be delivered. Each group meeting consists of a check-in period of 5 min, the reading of meditation instructions by the PI, 20 min of silent unguided meditation, 5–10 min of journaling about what arose for participants during the meditation, and a 5-min break. After journaling, each participant takes a turn and describes their meditation experience, with the PI offering empathic exploration. In emotion-focused mindfulness therapy, as in emotion-focused therapy, empathic exploration is a core competency that involves reflection, validation, responding to participants, and heightening their emotional experience [42, 43]. This is the process that is the heart of change and encourages participants to become more familiar with, and develop a tolerance to, distressing emotions [33].

EFMT poses little risk for participants. Meditation can sometimes cause uncomfortable feelings to arise when participants connect with emotions. Participants may decide to withdraw from the intervention if overwhelming emotions emerge. Participants may decline to answer questions during the reporting part of the meditation group. Should a participant become upset during any part of the group, the PI can: ask that participant to remain after the group to talk; ask that group participants take a short break while the PI speaks with the upset participant; lead the upset participant through a relaxation and grounding exercise; ask the participant if the PI may contact someone of their choice for support; and help the upset participant to access counseling. Participants may withdraw from the study at any time; however, study participants will be retained in the trial wherever possible to enable follow-up data collection and prevent missing data.

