### Outcome collection and measures

*Aim 1*. Determine if participants can be recruited, enrolled and retained

Recruitment, enrollment and retention data will be used to evaluate feasibility. Data will be gathered and measured on the number of potential participants referred and screened for eligibility, participants meeting eligibility requirements, participants enrolled, and participants completing the intervention. Recruitment and enrollment will be considered feasible if 70% of the total number of potential participants meeting eligibility requirements consent to enroll [44], and if 48 participants can be enrolled within a 3-month period (16 participants recruited per month). Retention will be considered feasible if 65% of participants complete data collection at both timepoints [45].Variables such as changes to medications, beginning, or stopping mental health counseling and significant life events will be tracked by the RA at T3 data collection timepoint. Extraneous variables will be important to gather to identify other potential reasons for changes to secondary outcomes aside from EFMT.

*Aim 2*. To determine if participants can adhere to all components of the intervention

Adherence will be used to measure acceptability. The intervention will be considered acceptable if 70% of participants attend of a minimum of six meetings [44]. As well, acceptability for measures of adherence to meditation, journaling, and reporting will be gathered through PI observation and documentation. Adherence to these components will be considered acceptable if the majority (75% or more) of participants appear to be meditating, journaling and actively report their meditations. Participants will not be required to practice between meetings; however, data will be gathered on the frequency and duration of home practice meditation and journaling to explore whether there is a relationship to outcomes. Participants will complete weekly reporting forms to be emailed to the PI. The PI will keep an observational diary noting what works well and perceived areas of challenge.

*Aim 3*. To determine the secondary objective of whether participants who receive the intervention potentially have decreased levels of anxiety compared to those participants who do not receive the intervention, the GAI will be used [35]. Outcome measures will be collected using the GAI at T1, T2 and T3.

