### Sample size justification

A sample size of 48 participants will allow for intervention group sizes of six participants and wait listed control group sizes of six participants. There will be four blocks of participants, with 12 participants in each block, and groups of six participants. This will result in 24 participants per arm. Small sample sizes of 10–20 participants or more are appropriate for pilot testing of adherence to interventions and this study will exceed those numbers, thereby allowing for attrition [48, 49]. There are also pragmatic considerations to selecting the sample size for this study [50], which include planning to complete the study within a year with limited funding. The study will not be powered to detect significant changes on the secondary outcomes. As COVID-19 protocols prohibit groups meeting in person, this study has moved to Zoom, an online privacy protected platform [51]. Other COVID-19 adjustments pivots required will be shorter meetings of 1.5 h to avoid Zoom fatigue and smaller group sizes [40]. This will be sufficient to meet the study’s primary objectives of recruitment, retention, and completion rates to determine whether a large study is warranted.

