### Feasibility and acceptability outcomes

Feasibility and acceptability outcomes will be determined by the following: recruitment and enrollment will be considered feasible if 70% of the total number of potential participants meeting eligibility requirements consent to enroll [44], and if 48 participants can be enrolled within a 3-month period (16 participants recruited per month). As a dropout rate of 35% is consistent with MBIs based in self-management and with a technology based delivery, a retention rate of 65% will be used to determine feasibility [65, 66]. Participants’ adherence to all components of the intervention will be defined by attendance of 6/8 sessions and participation in meditation, journaling, and reporting during the sessions, as observed and documented by the PI. In the tradition of MBI research, the intervention will be considered complete if participants are able to attend a minimum of 6/8 meetings [45]. It will be assumed that participants will be honest about meditation within the group, although direct evidence can only be inferred through observation [67]. Participants are not required to practice at home; however, they will be asked to self-report on the frequency and duration of home practice meditation and journaling to explore whether there is a relationship to outcomes.

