### Statistical methods

Data entry will be conducted by the RA. Data analysis will be conducted by the PI at the end of the study using SPSS V27 [68]. All data will be examined by running frequencies on each variable to determine if values are missing or out of range. Possible errors will be compared to raw data and corrected as necessary to ensure accuracy [67]. As is recommended for pilot feasibility studies, the following descriptive statistics will be used: for continuous variables, minimum, maximum, mean, median, mode standard deviation, skewness, and kurtosis; if continuous variables are skewed, non-parametric descriptive statistics will be reported; for categorical variables, frequencies will be used [69, 70]. Graphical displays such as histograms or boxplots will be presented to demonstrate and better understand the central tendency and dispersion of the data [67]. Recruitment, enrollment, and retention rates will be calculated. Rates of attendance and adherence to each component of the intervention will also be calculated to determine acceptability.

To examine whether there have been potential changes in the secondary outcomes, descriptive statistics will be used to analyze and present demographic and baseline data. Categorical and ordinal data will be compared using chi-square. Continuous data will be compared using a *t*-test. The mean change in the intervention group and wait list control group outcomes will be compared post intervention (T3) using an independent samples *t*-test, and Cohen’s *d* will be calculated for effect size [67]. Data from each of the groups will be combined to form a larger sample size to evaluate the effect of the intervention. Analysis of pooled data will be conducted using a paired sample *t*-test and Cohen’s *d* to examine the intervention effect over baseline measures. Change over time for the intervention group from T1 to T2 to T3 will be calculated by using repeated measures ANOVA to determine if change has occurred and/or is maintained in the intervention group.

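### The repeated measures ANOVA in its standard form keeps only participants with all three assessments, so at the plan's own retention threshold it would describe about 16 of 24 people and could misstate change and its maintenance if loss is related to response

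*Protocol article*

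**What the plan says.** Statistical methods names three analyses of change in the secondary outcomes.

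- Between arms: "The mean change in the intervention group and wait list control group outcomes will be compared post intervention (T3) using an independent samples" t-test, with Cohen's d.
- Pooled over arms: a paired t-test against baseline, with Cohen's d.
- Within the immediate-treatment arm: "Change over time for the intervention group from T1 to T2 to T3 will be calculated by using repeated measures ANOVA", to judge whether change occurred and whether it lasted.

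On missing data, that section says only that frequencies will be run to find missing or out-of-range values.

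On the amount of loss, Outcome collection and measures has "Retention will be considered feasible if 65% of participants complete data collection at both timepoints". Feasibility and acceptability outcomes gives the reason: "As a dropout rate of 35% is consistent with MBIs based in self-management and with a technology based delivery". On size, Sample size justification says "This will result in 24 participants per arm".

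On reasons for loss and efforts against it, Intervention description says "Participants may decide to withdraw from the intervention if overwhelming emotions emerge". It also commits to keeping participants in the trial for follow-up where possible. Collection of information at T3 has the research assistant try to assess everyone, whatever their attendance. Under Consent, a person who withdraws may have collected data destroyed.

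**The concern.** Repeated measures ANOVA, as standard software runs it, deletes listwise. An immediate-arm participant with T1 and T2 but no T3 contributes nothing, not even to the T1-T2 step for which both scores exist. The T1-T2-T3 profile is therefore that of people who stayed to the end.

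If those who improved least by T2 are less likely to give a T3 assessment, two errors follow. The completers' T1-T2 change is too large, because they were selected partly on it. Their T3 mean then falls back towards the true value, which looks like partial relapse. Both questions put to this analysis, whether change occurred and whether it was maintained, would be answered from a distorted profile.

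The Discussion says the findings will feed sample size calculations for a definitive trial. An effect size taken from completers and too large would make that trial too small.

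**Working it through.** **Inputs from the protocol article.** Four blocks of 12 and groups of six (Sample size justification). Retention threshold 65%, read here as completing both T2 and T3 (Outcome collection and measures). A 35% dropout rate from the literature (Feasibility and acceptability outcomes).

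**Plan's own figures.** 4 × 12 = 48 in total; 4 × 6 = 24 per arm; 1 − 0.35 = 0.65. All reproduce. No power calculation exists to reproduce.

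**Numbers analysed at the threshold, if loss is equal in the arms.** 0.65 × 24 = 15.6, about 16 people in the ANOVA. 0.65 × 48 = 31.2, about 31 overall.

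**Inputs that are assumptions.** The article gives no GAI standard deviation or correlation. Assumed: SD 4.5, correlation 0.6 between any two assessments, true change −3.0 at both T2 and T3.

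**Case A: random loss.** 85% reach T2 and 65% reach both. Completers are unbiased. Variance of one person's T1-T2 change = 2 × 4.5² × (1 − 0.6) = 16.2. With 15.6 people, SE = √(16.2/15.6) = 1.02. Simulation, in which the number of completers varies, gives 1.03 for completers and 0.88 for a likelihood analysis of all available scores. From the unrounded values, (1.029/0.885)² = 1.35, so the completers' variance is 35% larger.

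**Case B: loss after T2 depends on the observed T1-T2 change.** Same 85% and 65%; loss before T2 is random.

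| Log-odds of leaving per SD less improvement | Completers T1-T2 | Completers T1-T3 | T1-T2 overstated by | Apparent relapse T2-T3 |
|---|---|---|---|---|
| 0.5 | −3.47 | −3.24 | 0.47 | 0.23 |
| 1.0 | −3.81 | −3.40 | 0.81 | 0.41 |
| 1.5 | −4.05 | −3.50 | 1.05 | 0.55 |

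The likelihood analysis gives about −3.0 and −3.0 in each row. A fresh large-sample run gave completers −3.45/−3.22, −3.82/−3.41 and −4.05/−3.53, in agreement.

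**Case C: all 35% lost before T2, depending on the T1-T2 change that would have been seen.** True change −3.0.

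| Log-odds | Completers T1-T2 | Likelihood T1-T2 | Share of bias removed |
|---|---|---|---|
| 0.5 | −3.67 | −3.54 | 0.13/0.67 = 19% |
| 1.0 | −4.18 | −3.97 | 0.21/1.18 = 18% |
| 1.5 | −4.52 | −4.28 | 0.24/1.52 = 16% |

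Here loss depends on a score never observed, and the mixed model removes at most about a fifth of the bias.

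**Second set of assumptions for loss after T2.** On an SD scale, with correlations 0.5 with T1 and 0.7 between T2 and T3, true change −0.30, 35% lost at T3, and odds ratios for leaving of 1.5 to 3 per SD worse T2 score: the listwise set overstates the T1-T2 change by 0.07 to 0.16 SD and the T1-T3 change by 0.03 to 0.06 SD. An odds ratio of 1 gives no bias.

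**The case against.** **Silence on missing data.** A condensed article may leave the handling of missing scores to a fuller document, and the named tests could be run on imputed data. The article never says that anyone will be dropped. This is fair as to a missing-data rule in general. But the article does name the ANOVA, whose standard form works this way, and a better method can be named in the same sentence.

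**Follow-up commitments.** The plan undertakes to retain participants and to seek T3 assessments whatever the attendance. This stands as a reason why loss may be smaller. It does not alter how the tests treat the scores that remain missing.

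**The 35% figure.** A reader might infer that the plan forecasts 35% missing outcomes. It does not: the figure comes from the literature and justifies a feasibility threshold. It shows what loss the plan would accept.

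**Timing of distress.** The article ties overwhelming emotions to leaving the intervention, not the trial. In the immediate arm the sessions fall between T1 and T2, so loss from distress would come before T2. That is Case C, where the mixed model helps little. This stands and limits what can be claimed for the main fix.

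**Direction and reach.** A reader might infer that the results will overstate benefit, or that the between-arm comparison is biased in the same way. Neither is supported. Loss related to good response would reverse the sign, and the direction between arms depends on differential loss, for which no figure was calculated. Discarding usable scores is mainly a feature of the ANOVA; a T1-T3 t-test omits only people without one of those two scores.

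**Conclusion.** The point holds, with modest importance. The named ANOVA would rest on about 16 of 24 people at the plan's own success threshold, and it would set aside T1-T2 pairs already collected.

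Under the assumed SD, correlation and strength of dependence, response-related loss after T2 shifts the completers' T1-T2 change by about 0.5 to 1.1 GAI points and creates an apparent relapse of about 0.2 to 0.6 points. The lower end is about half of one standard error (0.47/1.03). The upper log-odds of 1.5 is a strong dependence, an odds ratio of about 4.5. With random loss the cost is precision alone.

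A reader might also infer that a mixed model restores the true change whatever the cause of loss. It does so only where observed scores explain the loss.

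The stakes are limited because the outcomes are secondary, the trial is not powered for them, and the feasibility criteria do not depend on them. They matter because the estimates are meant to inform a later trial.

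**What to change.** In Statistical methods, replace the repeated measures ANOVA with one likelihood-based linear mixed model per scale (GAI, PSQI, MMQ). Use T1, T2 and T3 as outcomes, means by arm and time, an unstructured covariance, and every available assessment from all randomised participants whose data may be used. The qualification is needed because Consent allows withdrawn data to be destroyed. Take the planned change contrasts from this model, and report the number of participants by arm at each timepoint.

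Add one sensitivity analysis in which those lost are assumed to have done worse by a stated amount. This is needed because the model cannot correct for poor responders who leave before T2.

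The cost is a few sentences of text and a little more analysis work with standard mixed-model software. No new data are required, and the descriptive reporting can stay as planned.

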### Design and setting

The study is a feasibility randomized controlled trial (RCT) using a wait list control trial design. Due to COVID-19 restrictions, this study has been adapted from in-person delivery to telehealth delivery via Zoom. The first 48 people to meet the eligibility criteria will be randomly allocated to receive EFMT immediately, or in 8 weeks from time of baseline assessment (1:1 allocation ratio). Data will be collected by a blinded to group research assistant (RA) at baseline (T1), 8 weeks following baseline (T2), and 16 weeks following baseline (T3). Participants will be recruited from primary care clinics and community organizations that provide support to older adults. The principal investigator (PI)/facilitator of the EFMT groups will be blinded to the results of outcome assessments until the end of the intervention phase of the study. The PI is a registered psychotherapist certified in delivering EFMT and will facilitate all groups.

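### The overall F test of the three-timepoint ANOVA cannot by itself show that change is maintained; the first arm's T3 minus T2 change with a confidence interval can address it

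*Protocol article*

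**What the plan says.** The last sentence of Statistical methods assigns change across T1, T2 and T3 to "repeated measures ANOVA to determine if change has occurred and/or is maintained in the intervention group". The analysis covers one arm only, the one treated immediately. Design and setting places T1 at baseline, T2 at 8 weeks and T3 at 16 weeks, so this arm finishes treatment at about T2, and T2 to T3 is its post-treatment follow-up.

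The sentence names no contrast or pairwise comparison and does not define maintenance. The same section ties its other tests to particular comparisons: an independent samples t-test between arms, and a paired t-test on the pooled arms against baseline, each with Cohen's d. It also plans means, standard deviations and graphs for continuous variables.

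**The concern.** Maintenance is a statement about what happens after T2, that is, about T3 minus T2. The overall F test asks a different question: whether the three means are all equal. It rejects when anxiety falls and stays down, and also when anxiety falls and returns to baseline. If the F test were read as the answer, a significant result could be reported as change that occurred and was maintained when only the first part was true.

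A second, smaller matter is missing data. The standard repeated measures ANOVA, as run in SPSS, uses only participants with all three values. Someone with T1 and T2 but no T3 would then be lost from the T1 to T2 change as well, although that change is fully observed for them.

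**Working it through.** **Inputs from the protocol.** Arm size: "This will result in 24 participants per arm" (Sample size justification). This reproduces from the stated blocks: 4 × 12 = 48, and 48/2 = 24. Retention threshold: "Retention will be considered feasible if 65% of participants complete data collection at both timepoints" (Outcome collection and measures). Applied to one arm, 0.65 × 24 = 15.6, about 16 completers. That threshold is a minimum for success, so n = 16 is a lower working case and not a forecast.

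**Assumptions.** The protocol gives no alpha, effect size, SD or within-person correlation for this analysis. I take alpha = 0.05, a T1 to T2 drop of d = 0.3 to 0.8 SD, and a correlation ρ of 0.5 to 0.7.

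**Step 1: the two patterns.**
- Fully kept (0, −d, −d): the mean is −2d/3 and the deviations are 2d/3, −d/3, −d/3. The sum of squares is (4 + 1 + 1)d²/9 = (2/3)d².
- Fully lost (0, −d, 0): the mean is −d/3 and the deviations are d/3, −2d/3, d/3. The sum of squares is (1 + 4 + 1)d²/9 = (2/3)d².

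The univariate F statistic does not use the order of the timepoints. Relabelling them in one simulated dataset left it at 2.836 each time.

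**Step 2: power under compound symmetry.** The noncentrality is λ = n × (2/3)d² / (1 − ρ), with 2 and 2(n − 1) degrees of freedom. For n = 24, d = 0.5, ρ = 0.5: λ = 24 × 0.1667 / 0.5 = 8.00.

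| n | ρ | d (SD) | λ | Power, fully kept | Power, fully lost |
|---|---|---|---|---|---|
| 24 | 0.5 | 0.3 | 2.88 | 0.293 | 0.293 |
| 24 | 0.5 | 0.5 | 8.00 | 0.687 | 0.687 |
| 24 | 0.5 | 0.8 | 20.48 | 0.981 | 0.981 |
| 24 | 0.7 | 0.5 | 13.33 | 0.896 | 0.896 |
| 16 | 0.5 | 0.5 | 5.33 | 0.489 | 0.489 |
| 16 | 0.5 | 0.8 | 13.65 | 0.892 | 0.892 |

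Intermediate patterns behave the same way. Half relapse (0, −d, −d/2) and continued gain (0, −d/2, −d) both give λ = 6.00 and power 0.555 at n = 24, ρ = 0.5, d = 0.5.

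**Step 3: without compound symmetry.** This used 20,000 simulated trials per case, d = 0.5, and AR(1) correlation of 0.7 between adjacent visits and 0.49 between T1 and T3. The power is no longer equal.

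| n | Test | Fully kept | Fully lost |
|---|---|---|---|
| 24 | Uncorrected F | 80% | 88% |
| 24 | Greenhouse-Geisser | 77% | 85% |
| 24 | Multivariate | 77% | 95% |
| 16 | Uncorrected F | 59% | 67% |

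In this case relapse is the pattern more likely to give significance.

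**Step 4: what the paired changes do.** With compound symmetry, ρ = 0.6 and d = 0.5, the T2 to T3 paired comparison is significant in 5% of trials under full maintenance and 75% under full relapse at n = 24 (5% and 55% at n = 16). T1 to T3 reverses this at n = 24: 75% under maintenance and 5% under relapse. These changes separate the patterns. A non-significant T2 to T3 test would still not establish maintenance, so an interval is needed.

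**Step 5: precision of T3 minus T2.** The half-width is t(0.975, n − 1) × √(2(1 − ρ)/n), in SD units.
- n = 24, ρ = 0.5: 2.069 × √(1/24) = 2.069 × 0.204 = 0.42.
- n = 16, ρ = 0.5: 2.131 × √(1/16) = 2.131 × 0.25 = 0.53.
- ρ = 0.7: 2.069 × √(0.6/24) = 0.33 (n = 24) and 2.131 × √(0.6/16) = 0.41 (n = 16).

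**The case against.** The strongest reply is that a repeated measures ANOVA is more than its overall F test. Follow-up contrasts are a usual part of it, and naming them is commonly left to an analysis plan, which is not shown. The protocol nowhere says that only the F test will be read, and the planned means and graphs would reveal a return to baseline. This stands. A reader might infer that the planned analysis cannot address durability at all, but the text supports that only for the overall F test.

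A reader might also infer that T3 exists to measure durability. It does not do so alone. Collection of information at T3 times the visit to the end of the wait-list arm's course, and Statistical methods uses T3 for the between-arm t-test. The Objectives list no durability aim.

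A third tempting inference is that the F test always gives the same result for maintenance and relapse. Equal power needs compound symmetry, as Step 3 shows.

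On missing data, the research assistant will try to reach everyone regardless of attendance. The pooled paired t-test against baseline need not depend on first-arm participants having T3. Both facts reduce the loss.

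Finally, the sample size section says the secondary outcomes are unpowered, and the Discussion disclaims hypothesis testing. That lowers the stakes, but it also favours estimates with intervals over an omnibus test.

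What remains is that the protocol does not merely omit a detail. It gives the maintenance question to a named procedure whose overall test cannot answer it.

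**Conclusion.** The point holds in limited form and is minor. The overall F test cannot by itself show maintenance. The equality of the between-time sums of squares is exact and needs no assumption beyond the two mean patterns. Equal power rests on compound symmetry. The direction of the difference under AR(1) rests on the one correlation structure tried. Effect sizes, correlations and alpha are all assumed.

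The loss from complete-case analysis cannot be sized from the protocol. If only 16 of 24 in the arm had complete data, at most 24 − 16 = 8 would be dropped, and only those among them with both T1 and T2 would be lost needlessly from that change.

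The documents do not show that a false durability claim would follow, since the planned descriptive output could expose a relapse. The feasibility conclusions are untouched.

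**What to change.** In the last sentence of Statistical methods:
- Base any statement on maintenance on the first arm's mean T3 minus T2 change, reported with T3 minus T1, each with a 95% confidence interval.
- Report T2 minus T1 in the same way.
- Use everyone with both values for each change.
- Label the T2 to T3 change as descriptive, because the wait-list arm is then in treatment and there is no untreated comparator.
- If the ANOVA is kept, state that it is not the basis for concluding that change was maintained.

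This costs a sentence or two of wording and no new data or visits. The price is candour about precision: the T3 minus T2 interval will be wide, so the durability statement will be modest.
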